**5. Communication of results to community members**

Following the completion of the study, the results of the disease surveillance will be communicated to all study participants at a meeting called for that purpose. If the intervention has been effective in reducing disease, households who received the placebo at the beginning of the study, will be given the effective filter.

**6. Data analysis**

Data will be recorded on an Excel spreadsheet and analysed in Stata software (version 9). The primary analysis will consist of comparing longitudinal prevalence of diarrhoea between the intervention and the control groups.

Secondary analyses include:

- Comparison of faecal coliforms (TTC per 100ml) in the water before and after filtration.
- Assessment of longevity of the filters
- Descriptive analysis of use and acceptability data

Diarrhoea prevalence will be analysed using appropriate statistical procedures which adjust for clustering within household and for repeated measures over time. Multivariate analysis will adjust for potential confounders (e.g. age, level of wealth etc). The quantitative outcomes will be analysed with appropriate parametric and non-parametric methods.

Sample size

The sample size required for meeting the primary objective of the study i.e. detecting a 30% reduction in diarrhoea prevalence among individuals from the intervention group compared to individuals from the control group was calculated based on the following assumptions: a significance level of 0.05 (two-sided), 80% power, a baseline prevalence of diarrhoea of 5%, a coefficient of variation of 2. The following formula was used:

**N** = [(0.84+1.96)2 x (sd02+sd12)] / (p0-p1)2 = **511** Individuals

Where:

- sd0 and sd1 are the standard deviation among the control group and intervention group respectively;
- p0 and p1 are the expected diarrhoea prevalences among control and intervention group.
- Standard deviations were obtained as following: sd0=0.05*2=0.1 and sd1=0.035*2=0.07.

In order to account for lost to follow-up (10%) and clustering of diarrhoea within household, the sample size will be 600 individuals in each arm. Assuming 5 persons per household on average, the number of households to be recruited in each arm is 120 households per arm so approximately 240 households in total.

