**B. Objectives**

The objectives of the study are (i) to assess the effectiveness of the LifeStraw Family household filter in preventing diarrhoeal diseases (ii) to determine the effectiveness of the LifeStraw household filter in reducing the bacterial load of drinking water and (iii) to evaluate the extent to which it is used correctly and consistently by, and is acceptable to, the target population (iv) finally, we will measure longevity of the filter as it is used in a field setting.

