***4. Outcome assessment***

Diarrhoea prevalence

Within one month of distributing the filters, field investigators will visit each household once a month (i.e. 12 visits per household during the overall follow-up period) to conduct a health survey. They will record for each household member, whether she/he had experienced any illness in the past 7 days, prompting a list of symptoms - in which diarrhoea is included - if no answer was spontaneously given. Repeated point prevalence has been shown as more valid and less resource-intensive method for estimating longitudinal prevalence compared with continuous surveillance (Schmidt, 2007). Formative research will be conducted prior to the intervention in order to explore local perception of diseases. Based on these findings, diarrhoea will be self-defined (Ross, 1994) or defined according to the standard WHO definition of 3 or more loose stools in a 24 hr period. Any medical conditions observed by field staff during visits will be referred to the local medical centre.

Microbial water quality, filter use and longevity

In each of the two groups, a random sample of households (25%) will be selected every month to assess microbiological performance of the filters. Field staff will conduct unannounced random visits and will take two samples: one sample of untreated drinking water before it is poured into the filter and one from filtered water coming out of the system’s tap. If the household store the filtered water for drinking, a third sample will be taken from the container in which filtered water is stored. During the visit, field investigators will also fill a brief observations checklist on the filter’s appearance and potential problems encountered with the filter. If the filter is no longer in use, the reason given by the user will be recorded. If the filter has clogged, the time at which the filter went out of service will be noted and the filter will be replaced by a new one. This will be used to assess longevity. All samples for microbiological analysis will be collected in sterile Whirl-Pack™ Bags. Samples will be placed on ice and processed within 4 hours of collection to assess levels of thermotolerant (faecal) coliforms. Microbiological assessment will be performed using the Oxfam-DelAgua Portable Water Testing Kit in accordance with the kit’s instructions.

Acceptability

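### The only bacterial-load analysis named compares water before and after filtration; objective (ii) concerns drinking water and also needs a comparison between the randomised arms.

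*Protocol*

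**What the plan says.** Section B (Objectives) of the protocol sets as its second aim "to determine the effectiveness of the LifeStraw household filter in reducing the bacterial load of drinking water". Correct and consistent use is a separate aim, (iii).

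Section 6 (Data analysis) states the primary analysis as "comparing longitudinal prevalence of diarrhoea between the intervention and the control groups". Under secondary analyses, the entry on bacterial load reads "Comparison of faecal coliforms (TTC per 100ml) in the water before and after filtration". It names no arms.

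Section 4 (Outcome assessment), under microbial water quality, filter use and longevity, describes the sampling:
- "In each of the two groups, a random sample of households (25%) will be selected every month to assess microbiological performance of the filters".
- At each unannounced visit staff take "one sample of untreated drinking water before it is poured into the filter and one from filtered water coming out of the system’s tap".
- Where a household keeps filtered water to drink later, "a third sample will be taken from the container in which filtered water is stored".
- "If the filter is no longer in use, the reason given by the user will be recorded". The text does not say whether any water is sampled at such a visit.
- For a clogged filter, "the time at which the filter went out of service will be noted and the filter will be replaced by a new one".

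Section 3 (Study intervention) reports that the placebo was shown in the laboratory not to remove pathogens. It also says that households will be advised to keep to their usual drinking-water practices.

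**The concern.** The objective and the named analysis answer different questions. The objective is about the water that households drink. The analysis is about the change in water that passes through a working filter. The two agree only if every household uses its filter and filtered water stays clean until it is drunk.

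The trial randomises a placebo filter and samples its water on the same schedule, so a randomised estimate of the effect on drinking water is within reach, but the protocol does not specify it. The evidence that the placebo is inert comes from the laboratory. In the field, only a between-arm contrast would remove changes common to both devices, such as handling or settling.

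Interpretation of the primary result is also at stake. Suppose diarrhoea shows no difference between arms. A large before/after reduction could not tell whether cleaner water failed to help or households were not drinking cleaner water. An as-randomised estimate for drinking water could be set directly beside the as-randomised diarrhoea result.

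**Working it through.** **No stated figure to reproduce.** The protocol gives no expected reduction, sample size or precision for the water-quality analysis. Its one sample-size figure, 511 individuals per arm, is for diarrhoea. The printed formula gives (0.84 + 1.96)² × (0.1² + 0.07²) / (0.05 − 0.035)² = 7.84 × 0.0149 / 0.000225 = 519.2, which is 1.6% above 511. Nothing here depends on it.

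**Objective and analysis side by side.**

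| Element | Objective (ii) | Analysis named in section 6 |
|---|---|---|
| Water | Drinking water | Water before and after filtration |
| Households | Not limited to users | In practice, those with an after-filtration sample |
| Comparator | Not stated; the trial has a placebo arm | The household's own untreated water |

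**Data available for a between-arm comparison.** Section 6 gives 120 households per arm, and section 4 samples 25% each month for 12 months. Assuming full retention:
- 0.25 × 120 = 30 households per arm per month
- 30 × 12 = 360 household-visits per arm
- 360 / 120 = 3 visits per household on average, so visits within a household are repeated measures

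**Illustration of size (assumptions, not figures from the documents).** Let R be the log10 reduction at the tap in users, q the share of sampled households not using the filter, and s the log10 lost to recontamination in storage, with all users storing when s > 0. Take the reduction in non-users as zero. Then

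mean log10 reduction in water drunk = (1 − q) × (R − s).

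With R = 3:

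| Non-use q | s = 0 | s = 0.5 |
|---|---|---|
| 10% | 0.9 × 3.0 = 2.7 | 0.9 × 2.5 = 2.25 |
| 20% | 0.8 × 3.0 = 2.4 | 0.8 × 2.5 = 2.0 |
| 40% | 0.6 × 3.0 = 1.8 | 0.6 × 2.5 = 1.5 |

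With R = 2, non-use of 20% and 40% gives 1.6 and 1.2 for s = 0, and 1.2 and 0.9 for s = 0.5.

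The before/after figure at the tap stays at R in every row. If the stored sample is taken as the after-filtration value, the figure becomes R − s. That captures storage but still does not respond to q.

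Only the scale of R can be related to the protocol. Section 1 requires sources above 1000 TTC/100 ml, and 3 log10 from 1000 leaves 1 TTC/100 ml. The background's 4-log figure is a laboratory result for viruses and does not fix R for coliforms in the field.

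**The case against.** The strongest reply is that the protocol's coliform entry is one line in a list of secondary analyses, with details left to an analysis plan that is not shown. Log transformation, repeat visits and covariates are ordinary analysis-plan matters, and their absence is no fault. Section 4 says that the sampling is meant to assess the microbiological performance of the filters, and a before/after comparison serves that purpose. Use is a separate objective with its own checklist and descriptive analysis. Replacing clogged filters closes one route to non-use.

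Much of this stands, and it rules out several stronger readings that a reader might infer:
- **That the analysis is confined to the filter tap.** Section 6 does not say so. Stored filtered water is also sampled and could count as water after filtration.
- **That non-users are excluded.** No such restriction is written. Their likely lack of an after-filtration value is an inference from section 4.
- **That the placebo arm is ignored.** It is sampled identically, and a before/after comparison within each arm is compatible with the text. What is missing is a stated between-arm contrast.
- **That non-use would go unreported.** It would appear in the description of use.
- **That settling or die-off counts as filter effect because the paired samples are different water.** The text can be read as one batch before and after, and gives no standing times.

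The reply does not remove the mismatch. The protocol does more than leave the analysis open: it names a comparison, and that comparison measures something other than objective (ii). In the same section it states a between-arm comparison for diarrhoea.

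**Conclusion.** The point holds as a mismatch between a stated objective and the analysis named for it. The before/after comparison is a valid measure of device performance. On its own it does not estimate the effect of being given the filter on the bacterial load of drinking water, because it cannot register non-use and names no comparison with placebo.

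The direction is conditional. With any non-use or storage recontamination, the before/after reduction at the tap exceeds the reduction in water drunk; with neither, the two agree. A reader might infer that the plan demonstrably overstates the effect, but the documents give no rates of use, recontamination or field removal that would show it. The 2.7–1.8 log10 against 3.0 is an illustration that rests wholly on assumed 3 log10 removal in users, none in non-users, and 10–40% non-use.

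This is a secondary objective. The primary diarrhoea analysis is already between arms, and no stated figure changes. The correction is worth making because most of the samples it needs are already planned in both arms.

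**What to change.** Add to the secondary analyses in section 6 a between-arm comparison, as randomised, of log10 TTC in the water the household is drinking at the visit, in all sampled households. Define that water as:
- the stored sample, if filtered water is stored;
- the tap sample, if filtered water is drunk directly;
- the untreated sample, if the filter is not in use.

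Allow for repeat visits to the same household. Adjust for the paired untreated log10 TTC where it is a separate sample. When the filter is not in use, the untreated sample is itself the outcome and cannot also serve as the covariate, so report the unadjusted between-arm difference as well. Keep the before/after comparison and label it device performance.

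One change is needed in section 4: state that the untreated drinking-water sample is taken even when the filter is not in use. The present text describes that sample as water about to enter the filter and does not cover this case.

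The cost is a sentence or two of analysis text, one field instruction, and a few extra samples if such visits would otherwise have yielded none. The reported reduction may be less favourable than the before/after figure.

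### The 600 per arm leaves a design effect of only about 1.04 for household clustering, so the stated 80% power holds only if the within-household correlation is about 0.01 or lower

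*Protocol*

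**What the plan says.** The sample size paragraph in Protocol section 6 (Data analysis) sets the target as "detecting a 30% reduction in diarrhoea prevalence among individuals from the intervention group compared to individuals from the control group". The assumptions are "a significance level of 0.05 (two-sided), 80% power, a baseline prevalence of diarrhoea of 5%, a coefficient of variation of 2", and the standard deviations follow as "sd0=0.05*2=0.1 and sd1=0.035*2=0.07". A two-sample formula for independent individuals is then applied, with 511 per arm printed as the result.

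The next sentence moves to the enrolled number: "to account for lost to follow-up (10%) and clustering of diarrhoea within household, the sample size will be 600 individuals in each arm". The household count follows: "Assuming 5 persons per household on average, the number of households to be recruited in each arm is 120", so about 240 households in total.

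No ICC or design effect is given, and the increase from 511 to 600 is not divided between loss and clustering. Households are the unit of randomisation (section 2), and illness is recorded for every household member (section 4). Section 6 commits the analysis of diarrhoea prevalence to "appropriate statistical procedures which adjust for clustering within household and for repeated measures over time".

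**The concern.** One increase is asked to cover two things. The loss rate and the household size are both stated, so the part left for clustering can be worked out, and it is very small.

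This matters because each household shares one filter and is allocated as a unit, and the outcome is an infectious disease among people who share water and sanitation. Some positive correlation between members is to be expected. The protocol accepts this by naming clustering in both the sample size and the analysis. The analysis will therefore carry whatever variance clustering brings, while the sample size makes room for almost none. What is at stake is the 80% power claimed for the trial's only primary comparison.

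**Working it through.** **Inputs, all from section 6 of the protocol.** p0 = 0.05; p1 = 0.035 (30% lower); sd0 = 0.10; sd1 = 0.07; z-values 1.96 and 0.84; loss 10%; 5 persons per household; 600 enrolled per arm.

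**Step 1: the plan's own figure.** (0.84 + 1.96)² × (0.10² + 0.07²) / (0.05 − 0.035)² = 7.84 × 0.0149 / 0.000225 = 519.2. The printed 511 is about 8 lower (1.6%). It is a small slip, so both bases are carried forward.

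**Step 2: remove the loss allowance.**
- From 519.2: 519.2 / 0.90 = 577, leaving 23 of the 600.
- From 511: 511 / 0.90 = 568, leaving 32 of the 600.

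**Step 3: design effect left for clustering.** This is 600 × 0.90 / N = 540 / N.
- From 519.2: 540 / 519.2 = 1.040.
- From 511: 540 / 511 = 1.057.

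**Step 4: largest ICC that this covers.** With equal households of 5, the design effect is 1 + (5 − 1) × ICC, so ICC = (design effect − 1) / 4.
- From 519.2: 0.040 / 4 = 0.010.
- From 511: 0.057 / 4 = 0.014.

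**Step 5: other ways to treat loss.**
- Multiplying by 1.10 instead of dividing by 0.90: 600 / (1.10 × 519.2) = 1.051, ICC 0.013; from 511, 1.067 and 0.017.
- Losses that shrink the mean household to 4.5: ICC = 0.040 / 3.5 = 0.011; from 511, 0.016.
- No effective loss at all: 600 / 519.2 = 1.156, ICC 0.039; from 511, 1.174 and 0.044.

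**Step 6: consequence if the ICC is higher.** With 540 retained per arm and design effect DE:
- power = Φ(√[(540/DE) × 0.000225 / 0.0149] − 1.96);
- the detectable relative reduction r at 80% power solves 7.84 × 4 × [1 + (1 − r)²] / r² = 540/DE, keeping the coefficient of variation at 2;
- enrolment needed per arm for 80% power is 519.2 × DE / 0.90, rounded up.

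| ICC (assumed) | DE | Power for 30% reduction | Reduction detectable at 80% power | Enrolment needed per arm |
|---|---|---|---|---|
| 0.01 | 1.04 | 80% | 30% | 600 |
| 0.05 | 1.20 | 74% | 32% | 693 |
| 0.10 | 1.40 | 67% | 34% | 808 |
| 0.20 | 1.80 | 57% | 38% | 1,039 |

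Unequal household sizes would raise the design effect further at any given ICC.

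**The case against.** Several points on the other side carry weight.

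- **The true ICC is unknown.** A reader might infer that the trial misses 80% power at any ordinary level of household correlation. The protocol does not support that. It gives no ICC for prevalence averaged over 12 monthly visits. Shared exposure makes a positive value plausible, while differences by age within a household could hold it down. Neither effect is quantified, so the power loss can only be stated conditionally.
- **People lost part-way may still contribute.** With 12 monthly visits and a repeated-measures analysis, early visits can count. If those lost contribute half their information on average (an assumption), the design effect available is 570 / 519.2 = 1.098 and the ICC covered is 0.024. The ceiling is about 0.04. This widens the tolerable range without making it large.
- **The coefficient of variation matters as much.** N scales with its square. At 1.9 the base is 519.2 × (1.9/2)² = 469 and the ICC covered is 0.038; at 1.8 the base is 421 and the ICC is 0.071. At 2.1 the base is 572, or 636 after loss, and 600 is too few even without clustering. The powers in the table are conditional on the protocol's value of 2.
- **Inference is protected.** The analysis adjusts for clustering, so a reader should not infer an inflated type I error or intervals that are too narrow. Only planned power is affected. Nor does the protocol say how a non-significant result would be read, so a claim that it would be taken as evidence against a 30% reduction is speculation.

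Two other defences fail. The coefficient of variation of 2 describes variation between individuals; it does not describe correlation between members of one household, and the protocol itself makes clustering a separate allowance. A separate analysis plan might state an ICC, but the protocol already fixes 600 and says that it covers clustering, and that statement can be tested from its own figures.

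**Conclusion.** The point holds in conditional form. The protocol's inputs support 80% power at 600 per arm only if the household ICC is about 0.01 or lower. The limit is 0.014 from the printed 511, and about 0.04 under the most generous treatment of loss. These limits follow by arithmetic from stated figures, given equal households of 5 and a coefficient of variation of 2.

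The powers of 74%, 67% and 57% show what follows if the ICC is 0.05, 0.10 or 0.20. They are not estimates of this trial's power. The error lies in presenting 600 as an allowance for clustering at 80% power when, after loss, it contains almost none and no ICC is given to justify that.

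**What to change.** Keep 240 households. In the sample size paragraph of section 6:

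1. Correct 511 to 519.
2. Replace the sentence on loss and clustering with the explicit calculation 519 × [1 + (5 − 1) × ICC] / 0.90, and state the ICC assumed and its basis.
3. Report what 600 per arm gives over a plausible ICC range, either as power for a 30% reduction (for example 74% at 0.05 and 67% at 0.10) or as the reduction detectable with 80% power (about 32% and 34%). Drop the claim that 600 covers clustering at 80% power.

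The cost is a change of protocol wording and a less favourable stated power. Recruitment, conduct and analysis stay as they are.
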